# Feasibility of an online intervention (STAK-D) to promote physical activity in children with type 1 diabetes: protocol for a randomised controlled trial

**DOI:** 10.1186/s13063-016-1719-0

**Published:** 2016-12-08

**Keywords:** Type 1 diabetes, Children, Self-efficacy, Physical activity, Intervention, Feasibility, Protocol

## Abstract

**Background:**

Regular physical activity has important health benefits for children with type 1 diabetes mellitus (T1DM), yet children and their parents face barriers to participation such as lack of self-efficacy or concerns around hypoglycaemia. Multimedia interventions are useful for educating children about their health and demonstrate potential to improve children’s health-related self-efficacy, but few paediatric clinics offer web-based resources as part of routine care. The Steps to Active Kids with Diabetes (STAK-D) programme is an online intervention grounded in psychological theory (social cognitive theory) and informed by extensive preliminary research. The aim of the programme is to encourage and support safe engagement with physical activity for children with T1DM. The aim of this research is to explore the feasibility of delivering the STAK-D programme to children aged 9–12 years with T1DM, and to assess the feasibility of further research to demonstrate its clinical and cost-effectiveness.

**Methods:**

Up to 50 children aged 9–12 years with T1DM and their parents will be recruited from two paediatric diabetes clinics in the UK. Child-parent dyads randomised to the intervention group will have access to the intervention website (STAK-D) and a wrist-worn activity monitor for 6 months. The feasibility of intervention and further research will be assessed by rate of recruitment, adherence, retention, data completion and adverse events. Qualitative interviews will be undertaken with a subsample of children and parents (up to 25 dyads) and health care professionals (up to 10). Health outcomes and the feasibility of outcome measurement tools will be assessed. These include self-efficacy (CSAPPA), objective physical activity, self-reported physical activity (PAQ), fear of hypoglycaemia (CHFS; PHFS), glycaemic control (HbA1c), insulin dose, Body Mass Index (BMI), health-related quality of life (CHU9D; CHQ-PF28), health service use and patient-clinician communication. Assessments will be taken at baseline (T0), 8 weeks (T1) and at 6-month follow-up (T2).

**Discussion:**

The goal of this feasibility trial is to assess the delivery of STAK-D to promote physical activity among children with T1DM, and to assess the potential for further, definitive research to demonstrate its effectiveness. Results will provide the information necessary to design a larger randomised controlled trial and maximise the recruitment rate, intervention delivery and trial retention.

**Trial registration:**

ISRCTN, ISRCTN48994721. Registered on 28 October 2016.

**Electronic supplementary material:**

The online version of this article (doi:10.1186/s13063-016-1719-0) contains supplementary material, which is available to authorized users.

## Background

Type 1 diabetes mellitus (T1DM) is one of the most common chronic diseases in childhood [1]. It is a serious illness, with rapidly increasing incidence and prevalence [1–4] and age-specific mortality double that of the general population [5]. In 2015, there were approximately 31,500 children under the age of 19 years with diabetes in the UK, the vast majority with T1DM [6]. Diabetes management is complex and costly in social, psychological and economic terms [7, 8]. Parents/carers^1^ of preadolescent children with T1DM are generally responsible for their child’s diabetes management and behaviours, making the transition from parental care to independent self-management a unique experience for children [9]. Treatment includes daily insulin injections, a healthy diet with carbohydrate monitoring and regular physical activity [10]. Poorly managed childhood diabetes can have significant lifelong consequences. Physical activity has specific benefits for diabetes control [11], reducing risk of diabetes complications and cardiovascular disease [12], reducing overweight and benefiting mental wellbeing [13]. Research has shown that children with T1DM are less active than their peers [14–17] and this can be associated with parental concerns about hypoglycaemia [18] and the exposure of chronically ill children to excessive fatigue [19].

Interventions to increase physical activity in paediatric T1DM have commonly focussed upon structured aerobic or resistance exercise training [11, 20]. These interventions work well for young people who are already active but for those children who are less active, promoting lifestyle physical activity (such as walking, active play, etc.) may be more appropriate [21]. Consequently, there is need for an intervention that encourages and supports safe engagement with physical activity for children with T1DM.

Our previous work highlights a need for theoretically-informed interventions which include psychological elements (and outcomes) [11]. Our studies have shown that parental fear of hypoglycaemia and children’s low confidence for physical activity (self-efficacy) are important barriers to being active for children with T1DM [18, 22]. Self-efficacy in particular is a critical element in increasing and sustaining physical activity levels [21, 23]. Parents have pointed to a lack of ‘digestible’ resources for physical activity promotion and health care professionals (HCPs) have similarly identified a lack of age-appropriate, evidence-based resources [24]. Consequently, intervention should be age-appropriate and build children’s self-efficacy for physical activity which is essential to enable sustained lifelong behavioural changes.

In the UK, the peak age for diagnosis of T1DM is between 10 and 14 years [25]. Interactive, multimedia interventions may be useful health promotion tools with children of this age, who are learning skills in self-managing their condition. Our previous research shows that HCPs support the concept of introducing interactive, multimedia resources focussed on behaviour change into the clinical care of children [26]. Multimedia interventions are useful for educating children about their health, demonstrate potential to improve children’s health-related self-efficacy, and could make them more able partners in face-to-face communications with HCPs [27].

Prior work has demonstrated that children with T1DM favour web-based information [28] and that they (irrespective of socioeconomic and ethnic background) are comfortable with electronic media [29]. Similarly, parents of this age group are receptive to the use of novel technologies to help manage their child’s diabetes [30]. Despite this, few paediatric clinics offer web resources for physical activity promotion as part of routine care, and technology-based interventions for children with T1DM are scarce. Existing resources are not developed for this age group; they tend to focus on ‘sport’ rather than physical activity and active lifestyles; or they focus primarily on the parent rather than the child [29, 31–35]. Computer or web-based interventions have shown to be feasible, acceptable [34, 35] and can be effective [36] in promoting physical activity in school-aged children. Consequently, there is potential for a dedicated, interactive resource specifically promoting physical activity in children with T1DM.

We have previously developed a theory-based physical activity intervention for children with chronic conditions called Steps to Active Kids (STAK) [21] which builds self-efficacy for physical activity. This includes educational materials for parents and children, a physical activity diary, group activity sessions and goal-setting strategies. This feasibility study, known as the SKIP trial (‘Supporting Kids with Diabetes in Physical activity’), will adapt and test the feasibility of these materials for use by children with T1DM [22] using an interactive, online resource called STAK-D (Steps to Active Kids with Diabetes). STAK-D is a web package delivering all aspects of STAK-D except the group activity sessions. It is intended to promote safe physical activity, build self-efficacy and reduce fear of hypoglycaemia. It includes interactive elements, including child and parent zones, physical activity tracking and goal-setting (with feedback), active role models, activity routines using video demonstrations, and a message board. It is also a medium through which parents and children can contact a diabetes professional for advice on physical activity with diabetes through an ‘Ask the Expert’ facility.

STAK-D is a complex intervention which has been designed for implementation as an adjunct to clinical care in T1DM management. It is targeted at children aged 9–12 years and their families. Targeting this age range is appropriate since participants are likely to have a level of independence commensurate with using computer-based packages at home (98%) [37] with support from their parents. Also, intervention is beneficial at this age since lifestyle behaviours which are adopted preadolescence are more likely to be sustainable and, therefore, to influence disease risk factors across the life course [38].

The STAK-D programme combines educational (information, physical activity guidance, safety information), behavioural (physical activities and activity tracking) and cognitive-behavioural (physical activity monitoring and goal-setting) strategies to promote children’s self-efficacy for physical activity. STAK-D draws upon social cognitive theory constructs of self-efficacy and observational learning [39]. The intervention targets children who have barriers to physical activity and aims to promote self-efficacy via observing role models, mastery experience and persuasion (via education). It provides general advice around regular blood glucose monitoring (e.g. before, during and after physical activities and regularly throughout the day) and healthy eating, which has been approved by diabetes specialists, but it does not give guidance on insulin dosage and administration or carbohydrate counting. For this, families are encouraged to contact their clinical team, either using the ‘Ask the Expert’ element of the website or at their standard clinic appointments.

In addition to the website, STAK-D utilises a wrist-worn activity monitor (PolarActive; Polar Electro Inc., Lake Success, NY, USA) to encourage activity monitoring and goal-setting behaviours. The site is password-protected and can currently only be accessed by research participants and personnel.

### Rationale

As there is no published data for the efficacy of a theory-based, online physical activity intervention for preadolescent children with T1DM, this research marks an important first stage in the development of an evidence base. This study will explore how feasible it is to deliver the STAK-D programme to promote self-efficacy for physical activity in this population, and its findings will inform the decision to run a future definitive clinical trial.

### Aim

The main aim of this study is to establish the feasibility of undertaking a definitive trial to investigate the effectiveness of STAK-D. The definitive trial will be deemed feasible if it is demonstrated that we can successfully identify, recruit and retain patients with T1DM, and the proposed study design and intervention are considered acceptable by patients, parents and clinicians.

### Study objectives

#### Primary research objective

The main objectives are to accomplish the following: (1) to estimate the likely recruitment rate of children and their parents, (2) to assess the willingness of the clinical staff to recruit participants, (3) to assess the willingness of eligible participants to be randomised, (4) to assess adherence and compliance to different elements of the intervention (including wrist-worn activity monitors), (5) to examine potential adverse effects of the intervention, (6) to test collection of health, clinical and economic outcome measures with the aim of informing the larger trial, (7) to explore reasons for loss to follow-up and (8) to access the overall acceptability of the intervention.

#### Secondary research objectives

A secondary research objective is to estimate the variability of self-efficacy for physical activity scores (e.g. pre-intervention to post-intervention change) and other outcome measures in order to inform decisions about primary and secondary outcomes for the larger-scale randomised control trial (RCT) and associated sample size calculation.

## Methods

The protocol has been prepared according to Standard Protocol Items: Recommendations for Interventional Trials-Extension for Newborns, Children, and Adolescents (SPIRIT-C) [40]. For the completed checklist, see Additional file 1.

### Study design

This study is a 6-month randomised feasibility trial. It is a two-arm, individually randomised, controlled feasibility trial comparing the use of the STAK-D programme to usual clinical care. A mixed-method process evaluation will be ongoing and explore rate of recruitment, adherence (pattern of intervention use), retention, data completion and adverse events. Qualitative interviews with key stakeholders (children, parents and HCPs) will explore satisfaction with the intervention and identify necessary improvements prior to proceeding to a definitive trial.

### Study setting

Participants will be recruited from two paediatric T1DM clinics in the UK. The intervention will be delivered via a website that can be accessed by participants remotely (at home) via multimedia devices.

### Selection of subjects

#### Inclusion criteria

Children aged 9–12 years who have been diagnosed with T1DM for at least 3 months and their parents will be eligible to take part in the study. They must be able to understand spoken and written English.

Children and parents eligible for the qualitative process evaluation will be those who have been directly involved with the intervention; eligible HCPs will have been directly involved in the clinical care of children in the intervention arm of the study and be familiar with the research processes; all must consent/assent to being involved in an interview.

#### Exclusion criteria

Children who meet at least one of the following criteria will be excluded: (1) recurrent hypoglycaemia (blood glucose level below 4 mmol/l occurring at least daily) or consultant concern indicating poorly managed diabetes (glycosylated haemoglobin (HbA1c) level >80 mmol/mol and/or testing fewer than four blood glucose levels/day on a downloadable meter) and (2) lacking the mental capacity to decide to take part in the study and to participate in it (based on the clinical team’s judgement in accordance with the Mental Capacity Act 2005 Code of Practice 2007).

### Interventions

#### Active intervention

The intervention will be delivered to participants randomised to the intervention arm by a health psychology researcher. The researcher will provide parents and children with login details for the STAK-D website, and conduct face-to-face orientation training with them to demonstrate the website components and assist them in setting physical activity goals. They will be encouraged to use the website for the duration of the study and for a minimum of 6 weeks. The researcher will provide the child with a PolarActive watch, together with verbal and written instructions for its use and guidance on how the activity data will be downloaded. All children in the intervention group will be provided with a supplementary leaflet signposting them to local events, services and facilities where they can engage in physical activity. Children will receive full access to all the intervention components for 8 weeks (Table 1). After 8 weeks until the 6-month follow-up (T1 to T2), participants will continue to have access to the website (Kid Zone and Parent Zone) and the PolarActive activity monitor, but they will no longer receive individualised feedback on their activity levels.

**Table 1 Tab1:** Components, content and theoretical underpinning of the Steps to Active Kids with Diabetes (STAK-D) programme

Component	Content	Theoretical underpinning
Kid Zone (website)	Physical activity information and advice, 5-a-day activity target, activity tracking, goal-setting	Outcome expectations Persuasion (education) Self-regulation (goal-setting, self-monitoring) Mastery experience
Street dance routine (website)	28 × 10-min dance sessions gradually developing into a complete dance routine	Vicarious experience (role model) Mastery experience Social support
Goal-setting (website)	Personalised goal-setting and goal feedback from researchers via the website Identifying facilitators and barriers to behaviour change	Self-regulation (self-monitoring and goal-setting) Social support
‘Ask the Expert’ (website)	A way for children/parents to contact a health care professional with questions about physical activity with diabetes	Social support Persuasion (education)
Messaging Board (website)	An area where children/parents can post messages, comments and questions to other children/parents	Social support Vicarious experience
Physical activity monitor (PolarActive)	Physical activity and step-count monitoring/tracking	Self-regulation (self-monitoring and goal-setting) Mastery experience
Parent Zone (website)	Information and advice around physical activity	Social support Vicarious experience (role model)

#### Control group

Participants in the control group will not receive the STAK-D intervention, but will continue with usual clinical care according to that available at the site from which they were recruited. Both participating sites operate under the same general standardisation of care; they both adhere to Global IDF/ISPAD Clinical Practice Consensus Guidelines [41], NICE guidelines for clinical care of diabetes in children and young people [42], and the UK National Health Service (NHS) national diabetes best practice tariff, which specifies requirements for the service. Quantifying usual care with regards physical activity is difficult, although our previous qualitative research suggests that lifestyle physical activity advice is limited in the current clinical care of children with T1DM [18, 24]. Usual care at each site will be described as part of this feasibility study following recommendations by Erlen et al. [43]; this will allow for accurate definition of usual care in future trial design.

#### Outcome measures

Outcome measures will be completed at baseline (T0), 8 weeks (T1) and 6 months (T2).

#### Primary outcome measures

The primary outcome measures for the feasibility study are as follows:Recruitment rateAn estimate of the number of eligible patients and likely uptake rate will be assessed. The response rate for mailed invitation will be compared to clinic (face-to-face) recruitment rates. Refusal rate and reasons for nonparticipation will be assessed. This will enable a prediction of recruitment rate, number of sites and length of time needed to recruit the required number of patients for a future trial. A recruitment rate of between 25 and 40% would be considered reasonable based on our previous research [22] and similar studies [44, 45]Adherence ratePattern of intervention use will be monitored to assess fidelity of intervention delivery. We will explore users’ activity by website and page visits, more or less commonly used elements, and engagement with goal-setting and activity tracking. We will assess user satisfaction with STAK-D (e.g. navigation, ease of use, technical issues) at 6 months. Acceptable compliance will be defined as the child using the online resources and tracking their daily activity (using the PolarActive watch). Noncompliance will be defined as the child’s failure to access the STAK-D website and track their physical activity over the intervention periodRetention rateRetention will be defined as the number of participants completing the STAK-D programme including all scheduled follow-up data collection (T0, T1 and T2) compared to the number started. A retention rate of at least 70% at each time point would be considered feasible based on our previous research [22] and similar studies [44, 45]Data completion rateCompletion of outcome measures will be recorded at T0, T1 and T2 (complete and partial or noncompletion with reasons, including time to complete). Measures will be determined acceptable to parents and children (in terms of literacy, cognitive ability and capacity to understand) if more than 70% are fully completed (indicating quality data), and reported participant burden is minimal.The feasibility of gathering routinely collected clinic data from patients’ electronic diabetes record (height, weight, HbA1c level and insulin dosage) at T0, T1 and T2 will be assessed. This will allow us to ascertain the proportion of our sample with complete clinical records, and whether records will be accessible to our researchers at specified data collection time points. Feasibility of collecting observational data in this way will be determined if more than 85% of the sample have complete clinical records availableAdverse eventsAny adverse events experienced as a result of participation in the intervention will be recorded and evaluated. Adverse events are defined as any serious negative outcome resulting from the physical activity undertaken as part of the STAK-D programme. Severe hypoglycaemia, i.e., a blood glucose level below 4 mmol/l requiring the help of another person to treat it, will be considered an adverse event in either group. Data from meter and pump downloads combined (and meter downloads alone for those patients not on insulin pump therapy) will be used for identification of hypoglycaemic episodes, as per usual care at our participating sites. To determine the likelihood of adverse events being associated with the physical activity undertaken as part of the STAK-D programme, we will record whether the frequency and/or severity of hypoglycaemic episodes increased during the intervention period. The occurrence of adverse events related to the intervention will be assessed and compared to the control group (see ‘Harms’ section for potential adverse events).

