### Assignment of interventions

#### Sequence generation

Consented participants will be individually randomised with a 1:1 allocation to receive either the intervention or usual care; no participant will receive less than standard care. The allocated treatment will be determined using the ‘Sealed Envelope Company’ randomisation service [56]. After receiving consent and assent, and collection of baseline data, the researcher will send an SMS text message to the ‘Sealed Envelope Company’, which will automatically randomise the participant to the intervention or control group.

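### Retention is defined by completing the STAK-D programme, which control families never receive, so it yields no usable two-arm rate to hold against the 70% threshold

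*Protocol article*

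**What the plan says.** Under Primary outcome measures, the article lists retention as one of its primary feasibility outcomes. Retention "will be defined as the number of participants completing the STAK-D programme including all scheduled follow-up data collection (T0, T1 and T2) compared to" those who began; the closing words are "compared to the number started", with no statement of what was started. The criterion follows: "A retention rate of at least 70% at each time point would be considered feasible".

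Study design describes a two-arm trial "comparing the use of the STAK-D programme to usual clinical care". Sequence generation states: "Consented participants will be individually randomised with a 1:1 allocation to receive either the intervention or usual care". Control group states: "Participants in the control group will not receive the STAK-D intervention, but will continue with usual clinical care". The Child measures section nevertheless has the activity watch worn at T0, T1 and T2 in both arms, and Data collection methods sets out the assessment visits without distinguishing arms.

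The Aim section makes the ability to retain patients one of the conditions for calling a definitive trial feasible. Adherence, meaning use of the website and tracking of activity, is a separate primary outcome in the same list.

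**The concern.** Throughout the article the STAK-D programme is the name of one arm, not of the trial. A control family that attends every visit has therefore not completed the programme and, by the stated rule, is not retained. The denominator is also ambiguous: it could be everyone who entered the trial, or only those who began using STAK-D.

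Two further features make the rule hard to apply. It combines programme completion with attendance, so a child who stops using the website but gives full data at T1 and T2 counts as lost. And it asks for all visits together, while the threshold is set for each time point.

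At stake is the pass or fail of a primary criterion for going on to a definitive trial. The Abstract says that the results are to supply what is needed to design that trial and to maximise its retention. That calls for the follow-up rate in both arms, separate from how much the website was used.

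**Working it through.** The 70% threshold is set by reference to earlier research, so there is no formula to reproduce. The check is what the definition can yield.

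**Inputs from the article.** Target 50 dyads and minimum 33 dyads to progress (Sample size); 1:1 allocation (Sequence generation); no STAK-D for controls (Control group); STAK-D access given after allocation to the intervention arm (Active intervention); threshold of at least 70% (Primary outcome measures).

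**Reading A: the denominator is all dyads who entered or were randomised.** Only the intervention arm can enter the numerator, so the maximum is (intervention dyads) / (all dyads), even if nobody is lost.
- 50 dyads: 25/50 = 50%.
- 33 dyads: 16/33 = 48% or 17/33 = 52%.
- Needed for 70%: 35/50, or 24/33 (23/33 = 69.7% falls short).

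For illustration, if 80% of each arm is followed up (assumed), true retention is 40/50 = 80%, but the literal rule gives 20/50 = 40%.

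**Reading B: the denominator is dyads who started STAK-D.** Controls leave both numerator and denominator, and the rate rests on about 25 dyads. A result of 18/25 = 72%, for instance, has an exact 95% interval of 51% to 88%. Because access follows randomisation, intervention dyads lost before first use are not counted. With assumed counts:
- 17 completers of 25 randomised: 17/25 = 68%, fails.
- Same 17, one dyad never starting: 17/24 = 71%, passes.
- 16 completers of 25, three never starting: 16/25 = 64% fails, 16/22 = 73% passes.

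Dyads that drop out after starting stay in the denominator on either reading; only losses before starting can escape it.

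**All visits against each visit.** Baseline data are collected before randomisation, so T0 says nothing about loss among randomised dyads, and the informative visits are T1 and T2. If at least 70% complete both, at least 70% complete each. The reverse does not hold: 70% at each visit guarantees only 2 × 0.70 − 1 = 40% at both. The all-visits figure is thus a stricter test than the stated criterion, and cannot by itself show whether that criterion is met.

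**Under a follow-up definition.** With all randomised dyads as the denominator and attendance in either arm as the numerator, 70% means 35/50 (exact 95% interval 55% to 82%) or 24/33. Reporting by arm matters: with assumed follow-up of 15/25 in the intervention arm and 21/25 in controls, the overall rate is 36/50 = 72%, but the intervention arm alone is at 60%.

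**The case against.** The strongest defence is that the authors meant completing the study and wrote the programme's name loosely. That T0 appears among the visits to be completed supports taking the number started as dyads entering at baseline, in which case no randomised dyad escapes the denominator. This is plausible, but nothing in the article says it, and with that denominator the literal numerator runs into the 50% ceiling. It is also fair that both arms are followed, that missing data are to be quantified with reasons, and that a detailed statistical analysis plan will precede analysis. The correct rates will therefore be computable. The difficulty is that the article itself fixes a definition and a threshold that do not match them.

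Three stronger readings are tempting but not supported.

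- A reader might infer that the 50% ceiling and the shrinking denominator act together. They belong to mutually exclusive readings: if only STAK-D starters count, full attendance gives 25/25 = 100%, and nothing fails by construction.
- A reader might infer that the all-visits wording makes the per-visit threshold impossible to check. It does not, since completion is recorded at each time point; the wording is a mismatch.
- A reader might multiply the retention threshold by the data-completion threshold (measures are acceptable "if more than 70% are fully completed (indicating quality data") and conclude that both could be met with under half of dyads giving full data. For a single measure this is not shown. With 35 of 50 retained, 24/35 = 68.6% fails the rule, so at least 25 must complete, which is 25/50 = 50%. With 24 of 33 retained, 17 are needed, which is 17/33 = 52%. That criterion also judges whether the questionnaires suit children and parents, so putting all randomised dyads in its denominator would count attrition as poor acceptability. It needs no change on this ground.

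**Conclusion.** The point holds for retention alone. Followed literally, the definition gives either a rate that cannot exceed about 50% (48% to 52% at 33 dyads) or one that omits the control arm and any intervention dyads lost before first use. Neither is a two-arm retention rate that can be judged against 70%. The ceiling rests on the article's own 1:1 allocation and sample sizes. The denominator examples rest on assumed counts and show only that a single non-starter can turn a fail into a pass. Because this is a primary outcome with a numerical criterion that bears on progression, it should be settled before the results are known.

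**What to change.** Replace the definition with this: retention at T1, and separately at T2, is the number of dyads providing that visit's data divided by all dyads randomised, reported overall and by arm, regardless of website use. Apply the 70% rule at T1 and at T2, that is, 35/50 at the target or 24/33 at the minimum recruitment. Move programme completion to the adherence outcome and report it only there, for the intervention arm.

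The cost is a paragraph of wording and no new data, since both arms are already assessed at these visits. The small downside is that reported rates may look slightly less favourable than a rate among STAK-D starters.
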